#### Duration

Immunizations will be given over the course of 7 weeks. All patients will be followed to Week 17 (Arm 1) or Week 25 (Arm 2). The longest duration of follow-up will be blood draws 29 (Arm 1) or 37 (Arm 2) weeks after study entry in selected patients with either clinical or immunological responses or adverse events. Patients who have completed at least 13 weeks (Arm 1) or 21 weeks (Arm 2) of the study will be considered to have completed the study, although all patients will be encouraged to remain in the study for the full 17 (Arm 1) or 25 (Arm 2) weeks.

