Arm 2 (placebo followed by vaccine):

Weeks 1, 3, 5 and 7 Either saline or vaccine vehicle alone (5% DMSO in sterile saline) is given SQ in single injections of 500 l. At week 9, 11, 13, and 15 autologous DCs co-cultured with apoptotic irradiated LNCaP cells are given SQ in single injections of 500 l. At each of these latter times, autologous DCs co-cultured with apoptotic irradiated LNCaP-M1 cells, as well as either saline or vaccine vehicle alone (5% DMSOin normal saline ) are given SQ in single injections of 500 l. On weeks 9 and 11, autologous DCs exposed to KLH are also given SQ. The SQ injections may be given +/- 3 days from the scheduled visit, with the exception that the first injection, which will be given on day 8 (preferably) or day 9 after the patient completes leukapheresis.

Administration of Vaccine

The DC/LNCaP vaccine is given approximately 6-8 cm from the axilla in the inner aspect of the upper arm. The DC/LNCaP-M1 vaccine is given approximately 6-8 cm from the axilla in the inner aspect of the patients’ contralateral upper arm. The administration site is prepared with betadine and alcohol swabs. Injection is given with a 25-gauge needle by superficial SQ injection (not in the fatty part). DCs exposed to KLH and either saline or vaccine vehicle alone may be given in the anteromedial thigh approximately 12-24 cm distal to the inguinal ligament.

Immunologic Studies

DTH: DTH will be performed at the Rockefeller University GCRC, concurrent with each vaccination and at 2 weeks, 10 weeks and in some patients, at 22 weeks post last vaccination. DTH reactions will be read at the Rockefeller University GCRC between 40-48 hours after implantation. Results will be recorded on the CRF.

Lymphoproliferative responses, ELISPOT and CTL: Assays will be performed at the Rockefeller University.

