##### Immunogenicity

The primary parameter of immunogenicity will be measurement of DTH responses. Secondary parameters include of assessment of T cell responses by measurement of lymphocyte proliferation, ELISPOT and CTL assays.

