###### Delayed type hypersensitivity (DTH) responses

At screening, patients will be assessed for DTH response to positive control antigens (a standard “anergy panel” to include candida, trichopyton and tetanus). Patients with no positive response to the anergy panel are not eligible for trial entry. Responses to one of the anergy panel antigens will be subsequently used as a positive control non-modulated antigen. Each antigen will be placed subcutaneously using a tuberculin syringe to inject a volume of 100 l.

DTH responses during the study will be to the control non-modulated antigen and to various vaccine components, specifically the control immunizing antigen KLH, and to aliquots of killed LNCaP cells and LNCaP-M1 cells, to DC/LNCaP cells and DC/LNCaP-M1 cells, and as negative controls, to DCs which have not been peptide pulsed and to saline. DTH response will be assessed by measuring the region of induration surrounding the injection site of each antigen. Each antigen will be placed according to a stereotyped grid, and induration will be read between 40 and 48 hours after injection.

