### Monitoring and follow-up.

Patients will be monitored intensively at the Rockefeller University Hospital following each vaccination. Patients will be monitored directly for one hour after each vaccination. Patients may stay longer or may be admitted as necessary or at the discretion of the PI. Antihistamines and epinephrine will be available for treatment, as appropriate, of any allergic reactions. The local injection site and draining lymph nodes will be monitored for inflammation and swelling. Patients receiving placebo will not receive DTH tests (other than saline), so as not to tolerize them to subsequent vaccination.

Possible local reactions that should be recorded include erythema and induration (measured using a flexible ruler and pain/tenderness, or warmth at the injection site). Local or systemic reactions will be noted on the case report forms.

In the event of a local or systemic reaction, patients will be monitored until the reaction has resolved. All grade 3 or more severe reactions will require immediate notification of a study physician. Monitoring will include direct supervision by nursing and physician staff, monitoring of vital signs and physical examination as needed, and other appropriate medical measures as deemed necessary.

During the week after each immunization, the subject will be examined or contacted by phone by the investigator or his designee to obtain local and systemic reaction data and to determine the subject’s clinical status. Instructions to subjects leaving the Rockefeller University GCRC post-vaccination will include directions and telephone numbers to use in the event of any unusual or severe sign or symptoms. Subjects reporting such symptoms should be seen in the Rockefeller University GCRC at the time of maximal symptoms, and will be followed up clinically until resolution of symptoms.

Interim outpatient visits will include history and physical examinations as well as monitoring of clinical laboratory studies, as detailed in the schedule of events. Between outpatient visits, for the first 7 days post immunization, a self-assessment questionnaire will be completed by the patient with instructions to notify the study team by phone if any systemic symptoms or unusual or severe symptoms are experienced.

Longer term follow up will be performed at graded intervals following vaccination (weeks 9, 13, 17 and possibly 29 in Arm 1, and weeks 17, 21, 25 and possibly 37 in Arm 2).

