#### Analysis of immunogenicity data.

Immunogenicity data will be tabulated and quantitated for each of the quantitative assays planned. These include proliferation assays, ELISPOT assays, and CTL assays. For example, we will correlate positive or negative responses (proliferation index > 5, ELISPOT T cell responses > 100 SFC/106 T cells, and CTL responses with % specific killing > 15%) with positive or negative responses to our positive control antigens (influenza M1) and, where available, to the prostate antigens PSMA and PAP.

For ELISPOT, CTL response, LPA and DTH, the primary analysis will be based on the change from baseline. Changes in baseline will be summarized by the median and 25th and 75th percentiles, and arms compared with the Wilcoxon rank sum test. Additionally, the longitudinal responses will be examined using generalized estimating equation analyses (to incorporate all the responses on a subject).

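### DTH is to be compared between arms on change from baseline, but Arm 2 has no placebo-phase change score for any vaccine antigen; the section should name a contrast the schedule can support

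*Combined protocol and SAP*

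**What the plan says.** Under Outcome Parameters, Immunogenicity, the protocol states: "The primary parameter of immunogenicity will be measurement of DTH responses". The Analysis of immunogenicity data section then sets one rule for all four assays: "For ELISPOT, CTL response, LPA and DTH, the primary analysis will be based on the change from baseline", summarised by median and quartiles, with "arms compared with the Wilcoxon rank sum test". It names no visit, no period and no baseline, and it makes no exception for DTH. A supporting GEE analysis is added "to incorporate all the responses on a subject".

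The relevant collection rules sit elsewhere:

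- Monitoring and follow-up: "Patients receiving placebo will not receive DTH tests (other than saline), so as not to tolerize them to subsequent vaccination".
- On-study evaluations, Immunologic Studies: DTH is done "concurrent with each vaccination and at 2 weeks, 10 weeks and in some patients, at 22 weeks post last vaccination".
- The DTH subsection under Immunogenicity: screening uses the anergy panel (candida, trichophyton, tetanus). Later, "DTH responses during the study will be to the control non-modulated antigen and to various vaccine components", namely KLH, killed LNCaP and LNCaP-M1 cells, and the two DC products, with unpulsed DCs and saline as negative controls. Readings are taken 40 to 48 hours after placement.
- Dosing Plan: Arm 1 is vaccinated at weeks 1, 3, 5 and 7. Arm 2 has placebo at those weeks and vaccine at weeks 9, 11, 13 and 15.
- Duration: the week 29 (Arm 1) and week 37 (Arm 2) blood draws are taken "in selected patients with either clinical or immunological responses or adverse events".

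**The concern.** A between-arm test of change from baseline shows immunogenicity only if one arm is unvaccinated over the interval in which change is measured. For DTH to the vaccine antigens, the rule protecting placebo patients from tolerisation removes exactly those readings. The analysis section does not acknowledge this.

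If the test is run as written, a null result could be read as absence of immunogenicity when both groups had been vaccinated. A positive result would reflect chance, or differences in timing between arms, rather than the vaccine. This matters because the Broad Objectives rely on DTH to show that the immunization was active, and rest the toxicity conclusions on that. If the window and baseline are left open, they would have to be chosen after the data are seen.

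Two smaller points arise in the same section. The cell-based assays have no stated window for the arm comparison. The GEE would also take in late visits at which patients are sampled because of their outcome.

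**Working it through.** The documents give no sample size, level, effect size or SD for DTH, so there is no figure to reproduce. The check is a calendar followed by illustrations.

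**DTH calendar.** Follow-up weeks are the last vaccination (week 7 or 15) plus 2, 10 and 22: 7+2=9, 7+10=17, 7+22=29; 15+2=17, 15+10=25, 15+22=37.

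| Week | Arm 1 | Arm 2 |
|---|---|---|
| Screening | anergy panel | anergy panel |
| 1 | vaccine antigens, with 1st DC vaccine | saline only (placebo) |
| 3, 5, 7 | vaccine antigens, with vaccines 2 to 4 | saline only (placebo) |
| 9 | vaccine antigens, 2 weeks after last | vaccine antigens, with 1st DC vaccine |
| 11, 13, 15 | none scheduled | vaccine antigens, with vaccines 2 to 4 |
| 17 | 10 weeks after last | 2 weeks after last |
| 25 | none scheduled | 10 weeks after last |
| 29 / 37 | some patients | some patients |

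**Which change scores exist.**

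- Placebo-controlled change over weeks 1 to 9: Arm 1 has it. Arm 2 has no antigen reading before week 9, so the comparison is 12 against 0.
- Matched time since vaccination: Arm 1 week 1 to 9 against Arm 2 week 9 to 17. Both intervals contain four DC vaccinations, so the expected difference is zero however immunogenic the vaccine is, period effects aside.
- Same calendar week, for example week 17: Arm 1 is 10 weeks after its last vaccine and Arm 2 is 2 weeks after. This test could reject, but what it would measure is time since vaccination.

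**Which level comparison exists.** At week 9, Arm 1 has had four DC vaccinations and Arm 2 has had none before that visit. Levels, though not changes, can be compared there between the randomised arms.

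**Size of the loss (illustration).** Assumptions: normal responses with unit SD, 12 per arm, exact rank-sum test, 20,000 replicates. The one-sided 10% level is borrowed from the PSA and toxicity calculations.

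| Assumed vaccine effect | Vaccinated vs unvaccinated | Vaccinated vs vaccinated |
|---|---|---|
| 0.5 SD | 45% | 9.7% |
| 1.0 SD | 86% | 9.7% |
| 1.5 SD | 99% | 9.8% |
| 2.0 SD | above 99.9% | 10.3% |

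At two-sided 5% the middle column is 19%, 61%, 92% and 99%; the right-hand column is about 4.5% throughout.

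**Power of a pooled paired analysis (illustration).** With a signed-rank test, 24 complete pairs, one-sided 10% and normal changes, power is 72%, 94% and 99% for mean rises of 0.4, 0.6 and 0.8 SD.

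**Late visits in the GEE (illustration).** Suppose the true mean change is zero, the early and late values of one assay correlate at ρ = 0.5, and only patients with an early value above c SD are sampled late. The observed late mean is then ρ·φ(c)/(1−Φ(c)):

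- c = 0: 0.5 × 0.798 = +0.40 SD
- c = 0.5: 0.5 × 1.141 = +0.57 SD
- c = 1: 0.5 × 1.525 = +0.76 SD

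**Cell assays.** Leukapheresis falls at week 7+6=13 for Arm 1 after vaccination and at week 8 for Arm 2 after placebo. If the assays use only leukapheresis cells, the natural placebo-controlled contrast is week 13 against week 8. On-study evaluations also refers to blood draws before vaccination. Which draws feed the assays depends on Table 2, which is not legible in the available text.

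**The case against.** The strongest reply is that the schedule still holds a randomised DTH contrast. The week-9 readings compare four DC vaccinations with none, and for KLH, which the protocol describes as a neo-antigen, the missing baseline matters less. That stands. A reader might infer that a before-after analysis is all the schedule allows, or that DTH cannot show immunogenicity in this trial; the documents support neither. The week-9 contrast is nonetheless not what the section specifies, because it compares levels rather than changes.

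Second, the section names no visits, so vaccine against vaccine is an inference about how the test would be run. This is correct, and the claim that power equals the test level holds only at matched time since vaccination. But no change-score version escapes the problem: the placebo-phase version has no Arm 2 data, and the calendar-week version compares timing.

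Third, On-study evaluations places DTH at each vaccination, and the Regimen section describes placebo injections as vaccinations, so placebo visits might be thought to include antigen DTH. The Monitoring section explicitly rules that out. The two passages need reconciling.

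Fourth, within-patient change is already to be summarised, so a response would not go unseen. True, but the only test named is between arms.

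Fifth, late sampling is triggered by clinical response or adverse events as well as immune response. The selection figures are therefore neither an estimate of bias in this trial nor GEE estimates; they show only that outcome-dependent sampling can shift late means.

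Sixth, immunogenicity is an additional objective, and the sample size rests on PSA and toxicity. This stands and limits the severity.

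**Conclusion.** The DTH analysis is wrong as written and should be fixed. On the text alone, 0 of 12 Arm 2 patients can have a placebo-phase change score for a vaccine antigen. A matched change-score comparison therefore carries no information on immunogenicity, and rejects at about its nominal level in the illustration. What is lost is the placebo-controlled change comparison, not all DTH information: a week-9 randomised comparison of levels and a within-patient analysis both remain available.

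The restriction on skin testing does not touch ELISPOT, LPA or CTL, which keep a possible placebo-controlled comparison. It would go too far to call a week 13 versus week 8 mismatch established, since that depends on which samples are used. The GEE point is secondary: inclusion of outcome-selected visits is clear from the text, but its size is not.

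All power and selection figures rest on assumed effect sizes, normality, complete data, correlation and selection rule. The PSA and toxicity outcomes and the sample size are unaffected.

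**What to change.** Amend the Analysis of immunogenicity data section before any unblinded look at the immunogenicity results:

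1. **DTH.** Replace the change-from-baseline arm comparison with two analyses.
   - (a) A rank-sum comparison of randomised arms on week-9 DTH levels, read at 40 to 48 hours: Arm 1 two weeks after its fourth vaccination, Arm 2 at its first DC vaccination.
   - (b) A signed-rank analysis of within-patient change from the DTH placed at the first DC vaccine (week 1 or 9) to two weeks after the last (week 9 or 17), pooled over vaccinated patients, with saline and unpulsed-DC sites as negative controls.
   - State the limits. In (a), Arm 2 has no antigen baseline, Arm 1 has had more prior skin tests, and Arm 2 receives vaccine at the same visit. Analysis (b) is not randomised.
   - Reconcile the DTH timing in On-study evaluations with the placebo rule in Monitoring and follow-up.
2. **ELISPOT, LPA, CTL.** State that the between-arm test uses Arm 2's placebo-phase change (for example week 0 to 8) against Arm 1's post-vaccine change at the closest available visit, and name that visit from Table 2.
3. **GEE.** Limit it to visits scheduled for all patients (through week 17 in Arm 1 and week 25 in Arm 2). Report weeks 29 and 37 descriptively, noting how those patients were chosen.

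The cost is analysis wording only. The readings are already scheduled, and no visit, dose or skin test changes.

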#### Biostatistical analysis.

The primary specific aim is to compare the clinical status during the first part of the study (before the cross-over) between the placebo and the vaccine group. As defined in CFR, Phase-I/II studies should address both acute toxicity and activity/efficacy. Accordingly, this comparison will be based on two primary outcomes:

(1) activity: relative change in PSA.

We do not use the term “efficacy” here, because we recognize that change in PSA is not a validated “surrogate” for clinical benefit. The primary manifestations of disease progression in prostate cancer are rising PSA values, new lesions on bone scan, new symptoms of disease, and, less frequently, an increase in measurable tumor mass. Several groups have shown the prognostic significance of post-therapy declines in PSA, leading to an NCI consensus group proposal of a set of guidelines for the use of post-therapy PSA that can be used in phase II trials to identify agents for further testing (Fazzari et al., 2000).

(2) acute toxicity: incidence and severity of an adverse events.

Although the variables will be combined to address the overall clinical status, the power calculations below address each of these aspects independently.

Size of relevant differences: For activity, we would like to have sufficient power to detect a 50% decline in PSA in the treatment group vs. no change in the placebo group. For toxicity, we would like to have sufficient power to detect a 50% incidence of severe adverse events (acute toxicity) vs. a 5% incidence.

Power vs. level: If there should be acute toxicity, we do not want to overlook this (false negative result). A similar argument holds for activity: as long as the treatment with apoptotic LNCaP-DCs is well tolerated, we would rather go on with the next trial, even if we would later find out that apoptotic LNCaP-DCs are not active (false positive result), than to risk delaying the development of an effective treatment (false negative result). Thus, we want to guarantee 90% power for the above differences at the 10% level. If we should see lower acute toxicity in the vaccine group (unlikely) or higher activity in the placebo group (also unlikely), our decision would be the same as if we would see no difference: we would reconsider the use of this vaccination in the treatment of advanced prostate cancer. Given this one-sided decision strategy we will further increase power by using one-sided tests.

Statistical model: As the form of the relationship between changes in PSA and clinical success is unknown, we will use a Wilcoxon-Mann-Whitney Ranktest to compare activity. For SAEs, the exact Fisher test will be used.

Sample size: To detect any difference with 90% power at the 10% level (one-sided) the WMW test’s chi-square distribution must have a non-centrality parameter of 8.2 under the alternative. By our inclusion criteria, all patients will have had rising PSA levels prior to study entry. Thus, for the power calculation, we assume that PSA continues to remain elevated or to increase over the 9 week study period for at least two-thirds of the patients in the placebo group. If the vaccination should be active, PSA should decrease in two-thirds of the patients in the vaccine group. If we assume that even the largest decline expected in the placebo group does not exceed 50%, then this corresponds to the consensus agreement that a 50% decline should be considered relevant (Bubley et al., 1999; Fazzari et al., 2000). Conservative scenarios of relevant differences in PSA responses between the vaccine and placebo group, yield sample sizes between 9 and 13. From a Bayes'ian perspective, none of these alternative hypotheses is unlikely. Thus, with a sample size of 12 per group we can expect at least 90% power for detecting relevant activity at the 10% level for changes in PSA.

Regarding toxicity, this sample size also guarantees a 90% power to detect an increase in the cumulative incidence of SAEs from 5% in the placebo group to 50% in the vaccine group at the 10% level (or a 80% power at the 5% level). A 40% cumulative incidence could be detected with 80% power at the 10% level (or a 90% power at the 20% level). If no SAEs are seen in the placebo group, three SAEs in the vaccine group yield a p-value of .109 (one-sided, exact). With one SAE in the placebo group, four and five severe adverse events in the vaccine group yield a p-value of .158 and .077, respectively.

This suggests the following conservative stopping rule for the study: After the third SAE in the vaccine group, the study is stopped if no SAEs have occurred in the placebo group until this time. After the fourth SAE in the vaccine group, the study is stopped unless more than one SAE has already occurred in the placebo group.

Benefit: For the final analysis, PSA markers and adverse event indicators will be combined to assess the overall benefit of the vaccination. We will compute marginal likelihood scores (Susser et al., 1998) based on the relative change in PSA and the highest adverse event category observed in each patient. SAEs will "overwrite" any benefit of the vaccination, while other adverse events will augment the benefit. Thus, if large declines in PSA are observed in patients with more adverse events, the overall benefit of the vaccination will be downgraded. On the other hand, if adverse events are predominantly observed among patients with increase in PSA, this strategy increases power.

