##### --Prior/Concurrent Therapy--

1. Recovered from toxicity of any prior therapy

2. Biologic therapy:

No prior autologous or allogeneic tumor vaccines

No concurrent other immunotherapy

3. Chemotherapy:

At least 4 weeks since chemotherapy

Not previously treated with more than 2 chemotherapy regimens

No concurrent chemotherapy

4. Endocrine evaluation/therapy:

3 rising PSA values at least 2 weeks apart

At least 2 weeks since concurrent corticosteroids (other than for replacement therapy for adrenal insufficiency)

Medical hormonal therapy to maintain castrate testosterone levels permitted

5. Radiotherapy:

At least 4 weeks since radiotherapy

No concurrent radiotherapy

6. Surgery:

Prior surgery allowed

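### The PSA power claim of at least 90% with 12 per group does not follow from the scenario as written, and the stated non-centrality of 8.2 should be 6.57 (a conservative slip)

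*Combined protocol and SAP*

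**What the plan says.** The passage is in the combined protocol and SAP, section 6.i.n (Data analysis), under Biostatistical analysis. Relative change in PSA before the cross-over is one of two primary outcomes there. For the analysis, "we will use a Wilcoxon-Mann-Whitney Ranktest to compare activity", and the plan adds that "we will further increase power by using one-sided tests".

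The sample-size paragraph sets 90% power at a one-sided 10% level and says that the test's chi-square distribution "must have a non-centrality parameter of 8.2 under the alternative". Its scenario has three parts:

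- PSA stays up or keeps rising "for at least two-thirds of the patients in the placebo group".
- PSA falls in two-thirds of vaccine patients if the vaccine is active.
- No placebo decline is larger than 50%.

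Unspecified conservative scenarios then "yield sample sizes between 9 and 13". The plan regards all of them as plausible and concludes that "with a sample size of 12 per group we can expect at least 90% power for detecting relevant activity". It gives no PSA-change distribution, no value of P (vaccine change lower than placebo change) and no sample-size formula.

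**The concern.** Two things do not fit. First, 8.2 is not the non-centrality for the stated level and power. Second, the power of a WMW test depends on P. Saying how many patients in each arm have a falling PSA, and capping the placebo falls, leaves P open. The guarantee of at least 90% therefore has no visible basis.

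The same section explains that 90% power was chosen to avoid missing real activity, and that seeing no difference would lead the team to reconsider the vaccine. If power is below 90%, the risk of wrongly giving up on an active vaccine exceeds the 10% that the plan accepts, and a null PSA result would be read as stronger evidence than it is.

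**Working it through.** **Inputs from the plan.** One-sided level 10%, power 90%, WMW test of two groups (1 df), 12 per group with 1:1 allocation, stated non-centrality 8.2, stated range 9 to 13 (read as per group). PSA falls in 2/3 on vaccine and in at most 1/3 on placebo (1/3 is used below unless stated), with placebo falls no larger than 50%. The shapes of the PSA-change distributions are assumptions, because the plan gives none.

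**1. Non-centrality.** NCP = (z for 1 - alpha + z for power)^2.

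- One-sided 10%, 90% power: (1.2816 + 1.2816)^2 = 6.57.
- Two-sided 10% (equal to one-sided 5%), 90% power: 8.56.
- Two-sided 5%, 80% power: 7.85. One-sided 5%, 80% power: 6.18.
- 2 df at 20%, 90% power: 8.11. Small-sample t version of the stated case with 22 df: 6.83.

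None reproduces 8.2. An NCP of 8.2 corresponds to 94.3% power at one-sided 10%, or 88.9% at one-sided 5%.

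**2. Effect of the slip on the range.** Required n is proportional to the NCP, and 6.57/8.2 = 0.801.

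- If 9 to 13 was built on 8.2: 9 x 0.801 = 7.2 and 13 x 0.801 = 10.4, so 8 to 11 per group. Twelve covers it.
- If 13 was built on 8.2, power at 12 is Phi(sqrt(8.2 x 12/13) - 1.2816) = 92.9%.
- If 13 is truly needed with 6.57, power at 12 is Phi(sqrt(6.57 x 12/13) - 1.2816) = 88.1%.

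**3. What 12 per group requires.** Noether's formula without ties is n per group = NCP/(6(P - 0.5)^2). With 6.57 and n = 12, P = 0.5 + sqrt(6.57/72) = 0.80.

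**4. What the written scenario gives.** Of all vaccine-placebo pairs, 2/3 x 1/3 = 2/9 have both falling, 2/3 x 2/3 = 4/9 only the vaccine patient falling, 1/3 x 1/3 = 1/9 only the placebo patient falling, and 1/3 x 2/3 = 2/9 neither. Let q be the chance that the vaccine fall is the larger when both fall. If rises are alike in the two arms, P = 4/9 + (2/9)q + (2/9)(1/2).

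- Falls of the same size in both arms, q = 0.5: P = 0.667.
- Vaccine falls uniform on 0-100%, placebo falls on 0-50%, q = 0.75: P = 0.722.
- Every vaccine fall beyond every placebo fall, q = 1: P = 0.778.
- Normal shift with 2/3 v 1/3 falling: P = 0.729.

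The table shows simulated power at 12 v 12. For continuous changes the exact one-sided WMW critical value was used (actual level 0.0989).

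| Assumed reading | P | Power at 12 v 12 | Noether n for 90% |
| --- | --- | --- | --- |
| Same size of falls in both arms | 0.667 | 55% | 39.4, so 40 |
| Vaccine falls 0-100%, placebo 0-50% | 0.722 | 74% | 6.57/(6 x 0.222^2) = 22.2, so 23 |
| Normal shift | 0.729 | 76% | 20.9, so 21 |
| Every vaccine fall beyond every placebo fall, rises alike | 0.778 | 88% | 14.2, so 15 |
| As the row above, but all non-decliners tied | 0.778 | 93% | no-ties formula does not apply |
| No placebo declines | 2/3 + (1/3)(1/2) = 0.833 | 96% | 9.9, so 10 |
| As the fourth row, with smaller rises on vaccine | 0.833 | 97% | 9.9, so 10 |

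The first four rows use only what the scenario says plus a distribution shape. The last three each add a condition that the plan does not give as the basis of its calculation.

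**The case against.** The strongest reply is that the plan errs on the safe side. An NCP of 8.2 is too large for the stated level, so it inflates the sample size. This stands. A reader might infer that the wrong parameter leaves the trial underpowered, but it works in the other direction.

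A reader might also infer underpowering from a range that reaches 13 when 12 are enrolled. The documents do not support that as a material shortfall. If the range came from 8.2, it rescales to 8 to 11; if 13 is right, 12 still gives about 88%.

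Nor should 55% be taken as the trial's power. That case lets placebo falls be as large as vaccine falls. It drops the plan's target of a 50% decline against no change, and it sets aside the purpose of the 50% cap on placebo declines. It is a pessimistic bound.

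Finally, some readings that the text permits do exceed 90%. The target contrast speaks of no change on placebo, which could mean tied non-decliners (about 93%, provided every vaccine fall also exceeds every placebo fall). The words at least two-thirds also allow for no placebo declines at all (about 96%). These readings stand as possibilities, so 90% is attainable. They do not rescue an unconditional claim, because the plan does not say that its calculation rests on them.

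One could add that the Objectives section makes safety the primary objective. That is so, but the Biostatistical analysis section still names PSA change as a primary outcome and attaches this power figure to it.

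**Conclusion.** The point holds in two parts of unequal weight.

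- **Non-centrality.** 8.2 is wrong for one-sided 10% and 90% power; 6.57 is right. This needs no assumption about PSA. The error is conservative and does not cause underpowering.
- **Power claim.** At least 90% power with 12 per group does not follow from the scenario as written. Under plain continuous readings power is about 55% to 88%, with 55% a pessimistic bound and 74% to 88% the range that gives vaccine falls some advantage in size or shift. The matching risk of missing an active vaccine is 12% to 26% in that narrower range, or up to 45% at the bound, against the 10% intended. Power of 93% to 97% needs conditions that the plan does not state.

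The power figures rest on assumed distributions. They show that the claim is conditional; they do not establish the trial's true power. The trial is not shown to be too small. What is shown is that its stated guarantee is unsupported.

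**What to change.** In the sample-size paragraph of the Biostatistical analysis section:

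1. Replace 8.2 with 6.57, or state the level and power to which 8.2 belongs.
2. For each scenario behind the 9 to 13 range, state the assumed PSA-change distribution in each arm, or the resulting P, and how ties are treated. Recompute the range from these.
3. Replace the unconditional claim with a short table of power by scenario at 12 per group, using the sponsor's own stated distributions. Note that about 90% power needs P of roughly 0.80 when there are no ties.

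The cost is wording and a short recalculation, with no added patients, visits or data. The downside is that the stated power becomes less favourable, and a null PSA result would have to be reported with that conditional power in view.
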